## Abstract

**Background:**

Patients with cerebellar malformations exhibit not only movement problems, but also important deficits in social cognition. Thus, rehabilitation approaches should not only involve the recovery of motor function but also of higher-order abilities such as processing of social stimuli. In keeping with the general role of the cerebellum in anticipating and predicting events, we used a VR-based rehabilitation system to implement a social cognition intensive training specifically tailored to improve predictive abilities in social scenarios (VR-Spirit).

**Methods/design:**

The study is an interventional randomised controlled trial that aims to recruit 42 children, adolescents and young adults with congenital cerebellar malformations, randomly allocated to the experimental group or the active control group. The experimental group is administered the VR-Spirit, requiring the participants to compete with different avatars in the reaching of recreational equipment and implicitly prompting them to form expectations about their playing preference. The active control group participates in a VR-training with standard games currently adopted for motor rehabilitation. Both trainings are composed by eight 45-min sessions and are administered in the GRAIL VR laboratory (Motekforce Link, Netherlands), an integrated platform that allows patients to move in natural and attractive VR environments. An evaluation session in VR with the same paradigm used in the VR-Spirit but implemented in a different scenario is administered at the beginning (T0) of the two trainings (T1) and at the end (T2). Moreover, a battery of neurocognitive tests spanning different domains is administered to all participants at T0, T2 and in a follow-up session after 2 months from the end of the two trainings (T3).

**Discussion:**

This study offers a novel approach for rehabilitation based on specific neural mechanisms of the cerebellum. We aim to investigate the feasibility and efficacy of a new, intensive, social cognition training in a sample of Italian patients aged 7–25 years with congenital cerebellar malformations. We expect that VR-Spirit could enhance social prediction ability and indirectly improve cognitive performance in diverse domains. Moreover, through the comparison with a VR-active control training we aim to verify the specificity of VR-Spirit in improving social perception skills.

**Trial registration:**

ISRCTN, ID: ISRCTN 22332873. Retrospectively registered on 12 March 2018.

## Background

Previous research has explored the involvement of the cerebellum in a wide range of motor and cognitive functions. In particular, there is a general agreement that the cerebellum plays a crucial role in detecting contextual regularities and sequence and in forming and updating internal models of external events [1–3]. Cerebellar neuroanatomical and topographical organisations, with a uniform neuronal structure but multiple functional connections with other brain areas, are in line with its role as an effective forward controller through internal models [4–6]. Indeed, it has been demonstrated that different populations of cerebellar cells encode for sensorimotor and non-sensorimotor predictions and for their violations [7–10]. Accordingly, this predictive computational mechanism has been generalised to multiple domains, from a simple eye-blinking response to complex social behaviours [2, 3, 11]. Importantly, the cerebellar contributes to different domains have been proposed as a unified theoretical framework that could shed new light on the complex pattern of motor, cognitive, linguistic and behavioural disorders identified as cerebellar cognitive affective syndrome (CCAS [3, 6, 12];).

Given the increasing weight attributed to prediction mechanisms in neurocognitive models of how we understand others’ intentions [13], recent studies have focussed on the role of the cerebellum in social cognition [14, 15], namely the set of mental processes that are needed to understand social interactions and regulate social behaviour [16]. Research has confirmed that cerebellar diseases are associated with alterations in crucial aspects of social cognition, such as theory of mind [17, 18] and emotional processing [19]. Through its connection with cortical areas involved in the mentalising networks [20], the cerebellum seems to play a critical role in sequencing other people’s behaviours, resulting in the formation of predictive internal models of social events that are then matched with external information [21, 22]. Thus, alterations of the cerebro-cerebellar loops in congenital cerebellar malformations may affect predictive mechanisms, resulting in the impaired ability to understand others’ intentions, social deficits, and autism-like behaviours [23, 24].

In this light, rehabilitation programmes for children and adolescents affected by congenital cerebellar malformation should not only involve the recovery of motor functions, but also of higher-order abilities, such as cognitive processing of social stimuli [25]. However, only few single-case studies have reported data concerning cognitive rehabilitation for patients with cerebellar diseases, either congenital [26] or acquired [27–30]. Crucially, none of these previous studies has focussed on social cognition and has exploited the boosting of the specific predictive abilities of the cerebellum in order to treat and rehabilitate the neuropsychiatric symptoms shown by patients with cerebellar dysfunction [31].

Virtual reality (VR) has been proposed as a useful tool for the assessment, treatment and rehabilitation of mental health disorders due to the embodied experience and natural sense of presence offered by this technology [32–34]). Recently, innovative interventions using VR have been proposed for social skills’ training in adult and paediatric patients with autism spectrum disorders (ASDs) [35, 36] and with schizophrenia [37]. Immersive VR appears to be a promising field for cognitive and socio-emotional rehabilitation, especially for the paediatric age group, because of its highly motivating and interactive nature [38, 39].

Here, we use the GRAIL VR laboratory (Motekforce Link, Amsterdam, Netherlands) to develop a brand-new social cognition intensive training (VR-Spirit) based on the specific computation exerted by the cerebellum in predicting others’ behaviour. The GRAIL technology has been developed for motor rehabilitation, specifically for gait analysis and training, and is equipped with a dual-belt treadmill, a motion platform and an integrated motion-capture system. VR environments are projected on to a 180° cylindrical screen running in synchronisation with the treadmill in order to create a natural optic flow. This system has been already adopted for the motor assessment and rehabilitation of paediatric patients [40, 41]. Furthermore, recent studies have indicated that immersive VR technology could be useful even in cognitive rehabilitation [42] and behavioural interventions [43, 44].

For the aim of the present project, we developed two different VR scenarios, namely ‘playground’ and ‘sweet stands’, respectively, for the training and for the evaluation sessions. Participants are engaged in a competition with one of four avatars, who are easily identifiable by their clothing and body cues, and they have to reach one of three pieces of recreational equipment (training) or one of three stands (evaluation) before the avatar. On each trial, the participants are given a score when they arrive before the avatar to the game/stand mostly chosen by themselves during the course of the session. Social scenarios have been designed to force the children to anticipate avatars’ movements, thus predicting their preference. Four avatars were created for each scenario and were associated with pre-established probabilities to prefer each game/stand, thus showing a clear preference for one of the objects. Four different sessions were generated in order to equally distribute probability associations between avatars and objects and were presented in the 4 days of each training week. Hence, the avatars have different probabilities in each session with the purpose of avoiding possible memory effects. Day by day, experimental group patients are expected to implicitly learn the associations between contextual cues (games/stand) and avatars’ intentions in that session and anticipate their choice. In other words, the paradigm that underlies our applications should specifically enhance the building of predictive internal models of others’ behaviour. Since a lack of this computation has been proposed to explain social deficits in patients with cerebellar dysfunction [15, 31] as well as in autism [45], boosting the building of internal models of others’ intention could improve social prediction with a likely impact on more general social cognition abilities.

## Methods/design

### Aim

The primary aim of the trial is to investigate the efficacy of a new, intensive, cognitive rehabilitation protocol in a sample of Italian patients aged 7–25 years with congenital cerebellar diseases. The hypothesis is that the VR-Spirit rehabilitation protocol should:
Enhance social prediction ability resulting in better understanding of other people’s intentions and behavioursFacilitate general-domain implicit-learning abilityIndirectly improve cognitive performance in specific domains (attention and executive functions, memory, visuospatial abilities, sensorimotor integration)Produce an amelioration of patients’ quality of life

Contextually to the primary aim, the study would verify the feasibility and acceptability of this rehabilitative intervention for the target population.

### Participants

Participants are children, adolescents and young adults aged 7–25 years with congenital cerebellar malformations and with a Full-scale Intelligent Quotient (FSIQ) greater than 45. Cerebellar malformations refer to anatomical abnormalities affecting the vermis and/or the hemispheres not due to acquired lesions and not associated with progressive pathologies. However, it is noteworthy that these patients could exhibit malformations in other cortical structures. As an example, patients with Joubert syndrome often present with malformations of the pontine and medullary areas [46]. Participants are recruited at the Child Neuropsychiatry and Neurorehabilitation Unit of the Scientific Institute, IRCCS E. Medea. With the aim of achieving the target sample size, associations of patients can be contacted. The following exclusion criteria have been adopted:
Severe sensorial, motor and/or behavioural problems that could interfere with the use of GRAIL technologyBeing simultaneously involved in a different cognitive rehabilitation treatment, to avoid excessive demands to children and possible interference on training adherence ratesHaving been involved in a different cognitive rehabilitation treatment in the last 6 months before training, to avoid confounding follow-up effects

Parents of all known potentially eligible patients are contacted telephonically by the attending physician and are informed about the aims and methods of the protocol. If they agree with the study, an administrative staff member contacts the parents to organise the recovery. Since participation in the trial has to be arranged according to other clinical needs (e.g. routine medical checks) of the patients and to parents’ availability, a variable time frame from 1 month to 1 year could occur before patients get access to the trial. Intervention assignment is carried out by a research assistant only when patients are admitted to the recovery. It is noteworthy that the administrative staff that attends to the recruitment and organises hospitalisation is blinded to group allocation. Before starting any study procedures, a research assistant provides a description of the material and procedures to parents and patients and asks them to sign an informed consent.

### Design

The study applies a single-centre, randomised, active-controlled trial design. Patients are allocated to one of two groups undergoing two different rehabilitation programmes through a stratified permuted block randomisation procedure [47]. Age and cognitive level (more recently available Full-scale Intelligent Quotient, FSIQ) are chosen as stratification factors. In particular, we consider two levels for age, corresponding to 7.0–12.9 and ≥ 13.0 years, and three stages for cognitive level consistent with, respectively, absence of intellectual disability (FSIQ > 80), from borderline intellectual functioning to mild intellectual disability (80 ≥ FSIQ ≥ 61) and from mild to moderate intellectual disability (60 ≥ FSIQ ≥ 45) (48). Doing so, six blocks are generated and within each block an estimated number of eight patients should be enrolled to achieve and overcome the established sample size. First, participants are allocated to a block depending on the two stratification variables. Second, patients are assigned to one of the two interventions according to specific permuted sequence. Details of the permuted blocks are reported in Table 1.

**Table 1 Tab1:** Stratified permuted blocks randomisation of the study

		Age	
		7–12.9 years	≥ 13.0 years
FSIQ	46–60	CCSSCCSS	SCSCSCSC
	61–80	SCCSSCCS	SSCCSSCC
	> 80	CSCSCSCS	CSSCCSSC

Legend: *FSIQ* Full-Scale Intelligent Quotient, *S* VR-Spirit training, *C* control training

Group 1 (S) receives the social prediction VR training for 2 weeks (four daily sessions in a week). In each 1-h session, 80 trials of the experimental programme and one of four motor games, selected among the applications available in the GRAIL, are administered; for each weekly session, a different game is administered in random order. Group 2 (C) receives a control VR training of the same duration (2 weeks, four 1-h sessions per week) as the experimental training; the control training involves, for each session, a navigational game and the daily repetition of all the four games from the GRAIL suite that are also presented, one per day, in the experimental session; the social prediction experimental programme is not presented in the control training.

Before the training (T0), a battery of neurocognitive tests from the Developmental NEuroPSYchological Assessment, 2nd edition (NEPSY-II [49, 50];) spanning different domains, and, specifically, social perception abilities, is administered to all participants. Both groups also receive a 10-min training of how to move within the GRAIL environment using a custom-made navigational application. Then, a pre-training evaluation through a VR game session, based on the same paradigm of the VR experimental training but in a different scenario, and a computer-based Action Prediction task [51] are administered. Moreover, at T0, both patients and parents compile questionnaires on quality of life (Tno-Azl (Netherlands Organisation for Applied Scientific Research Academic Medical Centre) Children’s Quality Of Life questionnaire (TACQOL), TNO Quality of life/LUMC, 2001 [52];) and parents also complete the Child Behaviour Check List (CBCL [53, 54];).

Performance at the VR tasks is monitored for all the sessions of the training period (T1). In order to verify and compare the effects of the experimental and control training sessions, at the end of the 2-week training (T2) all participants are re-evaluated with the same neurocognitive tests, the VR evaluation scenario and the Action Prediction task.

With the aim to investigate the far transferability of the effects, a follow-up evaluation is provided after 2 months (T3) with the same protocol used at T0 except for the GRAIL evaluation scenario. Details of the study design are set out in Fig. 1 according to the Standard Protocol Items: Recommendations for Interventional Trials (SPIRIT) Statement [55, 56] (see also Additional file 1).

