### Outcome measures

Primary outcome measure:
Social prediction ability: performance during the pre- (T0) and post-training (T2) evaluation in the sweet stands’ scenario; standardised beta-coefficients of the regression between accuracy and probability in the testing phase of the validated PC-based Action Prediction task administered before/after the intervention (T0, T2) and at the follow-up visit (T3)

Secondary outcome measures:
Social cognition: Theory of Mind Parts A and B and Emotion Recognition of the NEPSY-II testing batteryImplicit learning: accuracy and reaction time in the familiarisation phase of an Action Prediction taskExecutive functions (inhibition and flexibility): Inhibition test of NEPSY-IIVisual attention: Visual Attention test of NEPSY-IIVisuospatial and visual-perceptual abilities: Geometric Puzzle and Picture Puzzle tests of NEPSY-IIMemory: Memory for Drawings test of NEPSY-IISensorimotor functions: Finger-tapping of NEPSY-IIBehavioural problems: CBCL 6–18, Parent versionOverall functioning and quality of life assessed using the TACQOL questionnaire, presented in two forms: the self-compiled one and the parent-compiled one

To assess training feasibility:
Number of dropouts: number of children who renounce to complete the 2-week trainingNumber of sessions completed per child: total number of sessions performed in front of the total number proposed of eight sessions

To assess training acceptability:
Acceptability questionnaire: an ad-hoc questionnaire completed by participants and another one by their parents after training conclusion (T2) to assess subjective evaluation of training accessibility and efficacy. It is to note that the same questionnaires are fulfilled by the patients of the active control group and their parents

A psychologist, who is not blinded to the intervention assignment, administers all the neuropsychological tests and questionnaires and records the performance during the GRAIL sessions.

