## Trial status

This protocol has been applied to ISRCTN registry on 12 January 2018, registered on 12 March 2018 and last edited on 20 December 2018. Recruitment started in February 2018 and will be continuing until August 2020 and is currently recruiting.

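### The second half of every stratum's allocation list copies the first, and the decoded lists are published while recruitment is open, so upcoming assignments can be foreseen

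*Protocol article*

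**What the plan says.** The Design section of the protocol article allocates patients "through a stratified permuted block randomisation procedure", with two age levels and three FSIQ levels as strata. It adds that "six blocks are generated and within each block an estimated number of eight patients should be enrolled"; what it calls a block here is a stratum. Within a stratum, "patients are assigned to one of the two interventions according to specific permuted sequence". Table 1 gives an eight-letter list for each stratum, and its legend decodes the letters (S for "VR-Spirit training, *C* control training").

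On timing and people, the Participants section states: "Intervention assignment is carried out by a research assistant only when patients are admitted to the recovery". It also says that the administrative staff who handle recruitment and hospitalisation do not know the allocation. Outcome measures states: "A psychologist, who is not blinded to the intervention assignment, administers all the neuropsychological tests". The Discussion adds that the GRAIL therapist and the parents are not blinded either.

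Trial status reads: "Recruitment started in February 2018 and will be continuing until August 2020 and is currently recruiting".

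**The concern.** Random allocation protects the comparison only if nobody who influences entry or assessment can foresee the next assignment. Two features of the article work against this: the lists have a regular structure, and they are in print during recruitment.

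There is room for foreknowledge to act. The attending physician telephones the families, and the wait before admission runs from 1 month to 1 year. Age and the most recent FSIQ, which define the stratum, can be known before admission. If the order of entry followed the expected arm, the groups could differ from the start on any outcome. The Statistical methods section leaves the stratification factors out of the analysis because it trusts the allocation procedure to have balanced them.

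A second route is the baseline. Each outcome is analysed as a change from T0, so a T0 test given by someone who already knows the arm could shift that change.

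**Working it through.** **Inputs.** The six lists in Design, Table 1; the target of 42 (21 per group) in Estimation of sample size; the recruitment dates in Trial status.

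**Step 1: the plan's own figure.** 6 strata × 8 = 48 slots, each list with 4 S and 4 C. This reproduces, and it exceeds 42 by 6.

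**Step 2: structure of the lists.**

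| FSIQ | Age | List | Entries 1–4 | Entries 5–8 |
|---|---|---|---|---|
| 46–60 | 7–12.9 | CCSSCCSS | CCSS | CCSS |
| 46–60 | ≥ 13 | SCSCSCSC | SCSC | SCSC |
| 61–80 | 7–12.9 | SCCSSCCS | SCCS | SCCS |
| 61–80 | ≥ 13 | SSCCSSCC | SSCC | SSCC |
| > 80 | 7–12.9 | CSCSCSCS | CSCS | CSCS |
| > 80 | ≥ 13 | CSSCCSSC | CSSC | CSSC |

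The halves agree in 6 of 6 lists. Two S and two C can be ordered in 4!/(2!·2!) = 6 ways, and the six starting blocks are those six orders, once each. SCSCSCSC and CSCSCSCS are alternation.

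**Step 3: could this be chance?**
- Independent random blocks of four: a list repeats with probability 1/6, all six with (1/6)^6 = 1/46,656 ≈ 0.00002.
- One random block of eight per stratum: 8!/(4!·4!) = 70 orders, of which 6 have equal halves, so (6/70)^6 ≈ 0.0000004.

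On either reading the second halves were evidently copied, not drawn.

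**Step 4: what the repetition alone reveals.** Assume an observer who has not seen Table 1, knows that the first four repeat, and has seen the first four assignments in the stratum.
- All lists filled: 6 × 4 = 24 of 48 slots are certain (50%).
- Seven per stratum, total 42: 6 × 3 = 18 of 42 are certain (43%).

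For comparison, take best guesses in a random block of four. The chances of being right at positions 1 to 4 are 1/2, 2/3, 1/3 × 1 + 2/3 × 1/2 = 2/3, and 1. The sum is 2.83, and 2.83/4 = 71%. If the second four are known to copy the first, it is (2.83 + 4)/8 = 85%.

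**Step 5: what publication reveals.** A reader of Table 1 needs only the patient's stratum and the number already enrolled in it to read off the next arm. This is a single-centre trial, and the unblinded psychologist and therapist see past assignments, so that count is within reach of staff.

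**Step 6: assignment against T0.** Participants places assignment at admission. Design places T0 before the training. Neither says which comes first within the admission.

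**The case against.** The article states real safeguards. All known potentially eligible families are contacted, the wait is attributed to clinical needs and parents' availability, the staff who organise admissions are blinded, and assignment waits until admission. A condensed article may also leave custody of the list to the full protocol. These points stand as partial protection. They do not conceal a printed list, and they do not cover the attending physician, the research assistant or the psychologist.

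Several stronger readings are tempting but not supported:

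- **That assignment precedes T0 as written.** The order is not stated. Fig. 1 and Additional file 1, which might give it, are not shown. The arm could be known at T0; no more can be said.
- **That 48 of 48 assignments are known, or 32 of 48 without the table.** These count list slots, not patients. The target is 42, and the Discussion warns that strata may not fill. Patients assigned before publication were not exposed by the article, and their number is not given. The 32 (24 plus 8 forced endings in the first blocks, 2+1+1+2+1+1) requires an observer who knows block size and repetition from the outset.
- **That every change score is biased.** The VR evaluation score is saved by the software, and the Action Prediction index comes from a computer task. Examiner influence is more plausible for the NEPSY-II tests, which are secondary.
- **That concealment was absent throughout, or that the list was misused.** The article shows neither.

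**Conclusion.** The point holds in this form: the second half of each list is not randomised, and the complete decoded lists are public while patients are still being assigned. From publication on, each remaining assignment can be read off by anyone who knows the stratum and the count in it. Apart from publication, the repetition fixes up to 24 of 48 slots, or 18 of 42 with seven per stratum. Both figures are upper limits that assume the pattern is known.

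Selective order of entry could affect all outcomes, including the primary ones. Knowledge of the arm at T0 is possible but not established, and matters most for the examiner-administered NEPSY-II tests. The documents do not allow the size of any resulting bias to be estimated. The Discussion names lack of blinding and unfilled strata as limitations, but not predictability. Analysis cannot undo assignments made under a foreseeable sequence, so the change is worth making while patients remain to be assigned.

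**What to change.** For patients not yet assigned, replace Table 1 by unpublished, computer-generated lists per stratum, built from independently drawn blocks of varying size (2 and 4). Make them long enough not to run out: Table 1 stops at eight per stratum, and 42 patients over six strata already average seven.

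Have the lists held by an existing staff member who takes no part in recruitment, scheduling or assessment, or use sealed opaque envelopes. The administrative staff should not hold a readable list: they arrange admissions, and their blinding is the one safeguard the article states on the enrolment side. Open each assignment only after consent and completed T0 testing, and state that order in the protocol.

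Report how many patients were assigned under the old lists, before and after publication.

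The cost is a short amendment, two randomisation phases to describe, and the constraint that T0 must finish before the arm is opened. T2 and T3 testing would remain unblinded; this change does not address that.

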### Statistical methods

Demographic, clinical and neuropsychological variables of the two groups of patients are inspected through descriptive statistics. A *t* test and *χ*^2^ are used to assess the differences between the experimental and control training groups at baseline for continuous and categorical variables, respectively, thus allowing us to verify successful randomisation. For each outcome measure, we calculate the change between T0 and T2 (training effect delta) and between T0 and T3 (follow-up effect). Delta is calculated as the arithmetic difference between the second/third time points and the first time point. The delta values of the two groups for the primary outcome measure are compared using independent sample *t* tests (two-tailed). For the primary outcome measure, a Bonferroni correction procedure will be used to control for multiple comparisons. Multivariate analysis of variance will be used to explore differential effects of the trainings in the secondary outcome measures. As to what concerns missing data, a modified intention-to-treat analysis approach will be adopted, including in the analyses all the participants who had completed the pre- and post-treatment evaluation sessions, even if they had not completed all the training sessions. No imputation of missing data, however, will be used considering the limited sample size and observation points [58, 59]. The stratification factors (i.e. age and FSIQ), will not be considered in the statistical analyses, assuming that the stratification procedure has ensured a balanced distribution across the two groups.

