### Estimation of sample size

Estimation of sample size was based on the distribution of the standardized beta-coefficients of the regression between accuracy and probability in the PC-based, contextualised Action Prediction task in children with typical development (M = 0.154, SD = 0.215) and with ASD (M = 0.008, SD = 0.112), with a between-group difference of moderate-to-large size (Cohen’s *d* = 0.87; see Amoruso et al., 2019 [45]). Given the difference in the standardised beta-coefficient between children with typical development and with ASD, an increase of moderate effect size in this outcome measure should represent a clinically relevant improvement in the ability to form predictive models of others’ behaviour, with a likely impact on social deficits and autism-like behaviours shown by patients with cerebellar malformations. Thus, we estimated that a moderate increase (0.13 mean change or 0.8 SD) of the standardised beta-coefficient after as compared to before the experimental training had clinical significance. Accordingly, a final sample of 21 patients per group has been set for our study in order to detect a between-group difference (independent sample *t t*est, two-tailed) between the effects of the experimental vs*.* control training (T2 − T0) of moderate effect size (Cohen’s *d* = 0.8) with a power of 0.80 and an alpha level set at 0.05. The software G Power 3 was used for this estimation.

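### Table 1 ties the last letter of every block to the age group, so incomplete blocks tend to make the VR-Spirit arm older, while the analysis omits age on the ground that balance is ensured

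*Protocol article*

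**What the plan says.** The protocol article's Design section stratifies by two age levels (7.0–12.9 and 13.0 or more years) and three FSIQ levels. Within each of the six strata, "patients are assigned to one of the two interventions according to specific permuted sequence". Table 1 gives one eight-letter list per stratum (S = VR-Spirit, C = control):

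| FSIQ | Younger | Older |
|---|---|---|
| 46–60 | CCSSCCSS | SCSCSCSC |
| 61–80 | SCCSSCCS | SSCCSSCC |
| > 80 | CSCSCSCS | CSSCCSSC |

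On numbers, the Design section expects that "within each block an estimated number of eight patients should be enrolled to achieve and overcome the established sample size". The abstract "aims to recruit 42 children, adolescents and young adults with congenital cerebellar malformations", and under Estimation of sample size "a final sample of 21 patients per group has been set for our study".

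Under Statistical methods, the primary deltas are compared by independent-sample t tests. Age and FSIQ are left out, "assuming that the stratification procedure has ensured a balanced distribution across the two groups".

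The Discussion accepts that patient availability may leave some lists unfilled. It also plans to submit preliminary efficacy data once at least half the target sample has been recruited.

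**The concern.** Two S and two C can be ordered in six ways, and Table 1 uses each way once. They are divided between the age columns by their last letter: every younger block ends in S and every older block in C. Each younger order also has its exact S-for-C mirror image in the older column.

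A block stopped early lacks its last letters. Among younger patients the missing letter is then more often S, and among older patients more often C. The two shortfalls push the age mix of the arms in the same direction. They also offset each other in the arm totals, so equal arm sizes give no warning.

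Age was made a stratification factor so that it could be left out of the analysis. If the table itself tilts age one way, an outcome change that depends on age enters the S minus C comparison with a mostly predictable sign. Chance imbalance, by contrast, averages to zero over repeated randomisations.

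**Working it through.** **Inputs.** The six lists come from Table 1. The target of 42 (21 per arm) comes from the abstract and Estimation of sample size, and the expected 8 per stratum from the Design section. The spread of 42 patients over the strata is not stated, so it is treated as an assumption and varied. Whether the power calculation supports 21 per arm is a separate matter and is not used here.

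**The plan's own figures.** 6 × 8 = 48 places, which exceeds 42. Each list holds 4 S and 4 C, so 48 patients give 24:24.

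**Even fill.** Counting the first n letters of each list and adding over the three strata in each age column:

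| n per stratum | Total | Younger S/C | Older S/C |
|---|---|---|---|
| 4 | 24 | 6/6 | 6/6 |
| 5 | 30 | 7/8 | 8/7 |
| 6 | 36 | 8/10 | 10/8 |
| 7 | 42 | 9/12 | 12/9 |
| 8 | 48 | 12/12 | 12/12 |

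At 7 per stratum the arms are 21:21 and each FSIQ row is 7:7. The older share is 12/21 = 57.1% in VR-Spirit and 9/21 = 42.9% in control, a gap of 3/21 = 14.3 points.

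**Other fills of 42, at most 8 per stratum.** There are 462. Giving each equal weight, VR-Spirit has the larger older share in 87%, the arms are equal in 12%, and control is older in 1.5%. The mean gap is 6.0 points and the range is −4.8 to +14.5. Only 17 of the 462 (3.7%) reach 14.3 points.

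**Random fills of 42** (six equally likely strata, lists repeated when they run out; both are assumptions):

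| Scheme | Mean gap | Mean absolute gap | VR-Spirit older / control older |
|---|---|---|---|
| Table 1 | 7.2 points | 7.2 points | about 93% / 2% |
| Independent random blocks of four | 0 | 4.1 points | about 42% / 41% |
| Simple randomisation, 21:21 (half the patients younger) | 0 | 12.7 points | symmetric |

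Four unequal sets of stratum shares gave the same Table 1 picture: means of 7.1 to 7.3 points, with VR-Spirit older in 92–93% of runs.

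**At 21 patients** (half of 42), the Table 1 mean gap is about 15 points and VR-Spirit is older in about 98% of runs.

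**Effect on the primary comparison.** Let g be the difference in mean change between the age categories, in SD units. The protocol gives no value, so g is an assumption. With no treatment effect, the expected S minus C difference is g × (older share in S − older share in C).

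- Even fill, g = 0.5: 0.5 × 3/21 = 0.07 SD. This is 0.07/0.8 = 9% of the planned effect ("0.13 mean change or 0.8 SD"). The standard error at 21 per arm is √(2/21) = 0.31 SD, and the two-sided type I error becomes 5.6%.
- Even fill, g = 1: 3/21 = 0.14 SD, type I error about 7.4%.
- Average random fill, g = 0.5: 0.5 × 0.072 = 0.036 SD.

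**The case against.** The strongest reply is that the plan expects eight patients per stratum, where every age-by-arm cell is 12, and that the Discussion already concedes some lists may stay unfilled. Baseline comparisons of demographic variables are planned, so an age difference would be seen. The outcome is a change score, so age differences in level cancel and only age-dependent change matters. The gaps also lie within what randomly drawn blocks of eight can leave by chance (95% range about −14 to +14 points at 42).

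Much of this stands. It limits the size of the problem and rules out two stronger readings that a reader might infer:

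- *The age skew at 42 is fixed at 14.3 points.* The documents do not support this. That figure needs a near-worst fill that the protocol never states. Some fills balance exactly and a few reverse.
- *Stratifying by age achieves no more than not stratifying.* This would set the near-maximum of 14.3 against the average of 12.7 under simple randomisation. Average against average, the figures are 7.2 and 12.7.

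Three things are not answered. The target of 42 is below 48, so at least one list must stay incomplete at the target. The Discussion says that lists may not fill, but not that unfilled lists tilt one way by age. And a baseline test would not flag the tilt: 12/21 against 9/21 gives a Fisher p of 0.54.

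**Conclusion.** The alignment of block endings with age is a matter of counting and is certain. Its result is a tendency: short of 48 patients, the VR-Spirit arm will usually hold the larger share of the older age category. At 42 the gap averages 6 to 7 points over the fills examined and is at most 14.5 points when no list is exceeded. At the half-sample allowed for preliminary results it averages about 15 points.

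The statement under Statistical methods that stratification has ensured balance therefore does not hold for age. Leaving age out lets any age-dependent change enter the primary comparison with a mostly predictable sign. The bias is modest: about 0.07 SD at even fill if change differs by 0.5 SD between age groups, and about half that at the average fill.

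These sizes rest on the assumed fills and on the assumed age effect. They concern the two-level age category only; a difference in mean age cannot be derived. The point deserves correction because the fault is systematic and cheap to remove, not because it threatens the trial.

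**What to change.** 1. **Allocation.** For assignments not yet made, complete any block of four already open in a stratum. Then draw each later block order at random and independently in each stratum. Switching in mid-block could itself leave that block unbalanced. Blocks that are finished as printed keep their endings, so this step removes the tilt only from later blocks.
2. **Analysis.** Under Statistical methods, delete the assumption that stratification has ensured balance. Include the age and FSIQ strata as covariates in the primary comparison of the deltas. This is the main protection, because it also covers patients already assigned.
3. **Reporting.** Give the age-stratum by arm counts in the preliminary and the final report.

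The cost is a short amendment and a few degrees of freedom: one for age and two for FSIQ, which takes the error degrees of freedom at 42 patients from 40 to 37. No patients, visits or staff are added, and patients already assigned keep their arm.
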